### Incentives and Disbursement

All participants received US $30 for each comprehensive survey completed (baseline, 3, 6, 12, and 18 months) and US $10 for each short survey completed (9 and 15 months). Participants received US $20 for each self-collected HIV/PrEP test kit completed at baseline, 6, and 12 months. Participants in the PrEP4T and LS4TM arms received US $10 for each intervention session attended (6 sessions per intervention). The total compensation for participants was as follows: condition A (SOC; US $250); condition B (PrEP4T; US $310); condition C (LS4TM; US $310); and condition D (PrEP4T + LS4TM; US $370). Participants completing a qualitative interview at 9 months received an additional US $50.

Participants were compensated using ClinCard, a reloadable debit card that allowed study staff to add funds via an online portal as study activities were completed. ClinCards were mailed directly to participants’ preferred addresses after study enrollment.

In the final 6 months of this 5-year study, PrEP4T and LS4TM were offered to all participants regardless of study group assignment to gather implementation data; no compensation was provided during this period.

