### Assessments and Survey Measures

Participants completed online surveys at baseline and at 3, 6, 9, 12, 15, and 18 months (Figure 2). Comprehensive surveys, lasting approximately 30 minutes, were administered at baseline, 3, 6, 12, and 18 months. The 6-month survey also included an assessment of the intervention program completed after intervention delivery. Short surveys, focused on PrEP uptake and adherence and lasting about 15 minutes, were administered at 9 and 15 months. All surveys were hosted on REDCap, a HIPAA-compliant platform.

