
### HIV Testing, Biomarker-Confirmed PrEP Outcomes, and Specimen Collection Protocol

The primary outcome was biomarker-confirmed PrEP uptake, assessed via emtricitabine triphosphate (FTC-TP) and tenofovir diphosphate (TFV-DP) concentrations in DBS. FTC-TP/TFV-DP assays were used for TFV-containing PrEP regimens approved for this population. PrEP uptake was defined as the detection of any quantifiable drug concentration. Secondary outcomes were PrEP adherence, indicated by TFV-DP concentrations >700 fmol/punch (corresponding to ≥4 doses per week) [54], and PrEP persistence, defined as 2 consecutive DBS samples showing PrEP use. Thresholds were based on the emtricitabine/tenofovir disoproxil fumarate (F/TDF) regimen and adjusted as appropriate for participants using other TFV-containing PrEP formulations (eg, emtricitabine/tenofovir alafenamide, F/TAF).

Participants self-collected DBS samples for HIV testing and PrEP level assessment at baseline, 6, and 12 months. Biospecimen processing was conducted by Molecular Testing Lab (MTL), a CAP-accredited and Clinical Laboratory Improvement Amendments–certified laboratory specializing in at-home specimen collection and processing. Participants provided a mailing address, which was validated through the US Postal Service Address Information application programming interface, and home specimen collection kits were shipped via the US Postal Service. Each kit included detailed visual instructions for specimen collection and a prepaid return mailer. Video instructions were available on the study website to guide participants through specimen self-collection. Each kit included a finger stick device, alcohol wipe, adhesive bandage, a Whatman 5-spot DBS card for HIV testing, and a Whatman 2-spot DBS card for PrEP adherence testing. Participants collected their specimens and returned the cards to the laboratory using the self-addressed, stamped envelope provided in the kit.

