### Statistical Analysis

#### Power

Factorial trials can be powered to detect either main effects or interaction effects, depending on the anticipated influence of interactions within the trial context [92]. This trial was powered to detect the main effects of the PrEP4T and LS4TM interventions. The trial was not powered to detect a PrEP4T × LS4TM interaction effect because (1) based on our conceptualization, the interventions were distinct in delivery (individualized vs group based) and content (peer navigation vs. community support and IMB strategies), and informed by preliminary studies and knowledge of the study population, we did not anticipate a combined interaction effect; and (2) any potential interaction was expected to be negligible, described in factorial trials as a minor “small quantitative interaction” [92-94]. Both PrEP4T and LS4TM were distinct, peer-delivered digital interventions that TMSM endorsed for HIV prevention in our prior research. We hypothesized that each strategy would independently increase PrEP uptake by at least 20% among TMSM, addressing the main-effects research question. Although we did not anticipate interaction effects, we hypothesized additive effects such that participants assigned to the PrEP4T + LS4TM condition would achieve the highest PrEP uptake rates. These superiority hypotheses were supported by evidence from a systematic review of peer-delivered interventions [47].

We estimated PrEP uptake rates in the SOC condition based on prior TMSM data [8,15] and conducted simulations using an SAS macro [95]. Simulations varied the number of participants per condition (n=40-120) and the magnitude of intervention effects over 18 months (20%-40%) for the PrEP4T and LS4TM conditions. Assuming 10% attrition, a total sample size of 300 (75 per condition) provided 80% power or greater to detect a 20% increase in PrEP uptake for each intervention versus SOC at a .05 significance level. We selected a 20% increase because smaller differences were not considered clinically meaningful for potential scale-up. To account for attrition, we planned to enroll 375 participants at baseline, anticipating approximately 20% loss to follow-up, resulting in 300 participants completing the study.

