#### Data Analysis by Aim

We describe the planned analyses by aim.

Before analyses, data will be audited for quality and completeness. Descriptive statistics will be calculated, and variable distributions will be evaluated to ensure they meet the assumptions of planned analytic models, including detection of outliers. In this study, *t* tests and chi-square analyses will be used to assess group equivalence at baseline. Variables showing differences across the 4 groups will be considered for inclusion as covariates in the analyses. All analyses will be conducted using SAS (SAS Institute) or R (R Foundation) software, with statistical significance set at an α level of .05.

Aim 1 analyses will follow an intention-to-treat approach. Random-effects logistic regression will be used with PrEP uptake as the primary outcome. The model will include time (baseline, 6, 12, and 18 months), a categorical variable for study condition (PrEP4T, LS4TM, PrEP4T + LS4TM, with SOC as the reference), and the time × study condition interaction to test whether changes in PrEP uptake over time differ across the 3 intervention conditions compared with SOC. Baseline characteristics that differ across study conditions, as well as variables related to missingness, will be included as covariates if necessary. The primary parameter of interest is the time × study condition interaction term; a significant interaction would indicate that the rate of PrEP uptake over time differs between the intervention and SOC groups. Significant interactions will be graphed and interpreted. We hypothesize that PrEP uptake will be highest among participants randomized to condition D (PrEP4T + LS4TM). The same analytic approach will be applied to the secondary outcome of PrEP adherence. PrEP persistence will be assessed at months 12 and 18 using random-effects logistic regression, including time (12 and 18 months), study condition, and the time × study condition interaction. HIV and sexually transmitted infection incidence will be evaluated using logistic regression, with incidence between baseline and 18 months as the outcome and study condition as the predictor.

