As of March 20, 2025, 103 TMSM were enrolled (Table 5). The median age was 26 (IQR 24-31) years. Among the 103 participants, 39 (37.9%) identified as BIPOC and 18 (17.5%) identified as Latine. The most frequently reported gender identities were “transgender men or trans man” (36/103, 35%); transmasculine (31/103, 30.1%); and nonbinary, genderqueer, or gender nonconforming (15/103, 14.6%). The majority of participants had socially, legally, and medically affirmed their gender identity. Participants reported diverse sexual orientation identities, with 67 (65%) identifying as queer, 38 (36.9%) as bisexual, 37 (35.9%) as gay, and 18 (17.5%) as pansexual (totals exceed 100% due to a “select all that apply” response format). The sample was highly educated: 69 (67%) had a 4-year college degree or higher, and 24 (23.3%) were full-time students. A small proportion (7/103, 6.8%) reported having no health insurance.

**Table 5 table5:** Sociodemographics of enrolled participants (N=103).

Sociodemographics		Values
Age in years, median (IQR)		26 (24-31)

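### The open offer of both interventions in the study's last 6 months is set by calendar time, with no stated condition that a participant's own follow-up is complete, so late enrolees could cross over before their last outcome visits

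*Protocol article*

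**What the plan says.** Under Incentives and Disbursement, the protocol article says: "In the final 6 months of this 5-year study, PrEP4T and LS4TM were offered to all participants regardless of study group assignment". The sentence continues with the purpose, "to gather implementation data; no compensation was provided during this period". No other section limits the offer to people who have finished their own follow-up.

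Follow-up lasts 18 months: "Participants completed online surveys at baseline and at 3, 6, 9, 12, 15, and 18 months" (Assessments and Survey Measures). Blood spots stop earlier: "Participants self-collected DBS samples for HIV testing and PrEP level assessment at baseline, 6, and 12 months" (HIV Testing, Biomarker-Confirmed PrEP Outcomes, and Specimen Collection Protocol).

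Data Analysis by Aim specifies an intention-to-treat analysis with standard of care (SOC) as the reference. Its primary model runs to month 18 ("The model will include time (baseline, 6, 12, and 18 months"), and "The primary parameter of interest is the time × study condition interaction term". The same section also uses month 18 for persistence and for HIV and sexually transmitted infection incidence.

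On numbers, the Power section says "we planned to enroll 375 participants at baseline", so as to finish with 300. Recruitment and Enrollment reports: "As of March 20, 2025, 103 TMSM were enrolled".

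**The concern.** A fixed calendar date for opening the interventions is harmless only if every participant has passed the last outcome visit by then. The rule does not require that.

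A participant still in follow-up when the offer opens could take up an intervention outside the assigned arm and then contribute outcome data under the original assignment. Arm A could receive either intervention, arm B could receive LS4TM, and arm C could receive PrEP4T. The PrEP4T margin (B and D against A and C) is diluted when A or C takes PrEP4T. The LS4TM margin (C and D against A and B) is diluted when A or B takes LS4TM. The D against A comparison is exposed to both. So the issue is wider than SOC alone.

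If the interventions work, the bias is towards no difference. Because it falls on the latest visits, it acts directly on the time-by-condition term that the plan names as primary.

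**Working it through.** **Inputs from the article.** Study length 60 months; open offer in the last 6; follow-up 18 months; last blood spot at month 12; enrolment target 375 (Power) or 300 (Table 1); 103 enrolled by 20 March 2025; enrolment start 1 February 2024 (Recruitment and Enrollment) or 1 April 2024 (Abstract). The two start dates disagree, so both are carried through.

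**The plan's own figure.** 300 / (1 − 0.20) = 375, which reproduces the planned enrolment.

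**Cutoffs.** The offer opens at 60 − 6 = month 54. The last safe enrolment is month 54 − 18 = 36 for the 18-month visit and 54 − 12 = 42 for the 12-month blood spot. Both are needed, because the primary model includes month 18 while the listed blood spots end at month 12.

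**Accrual.** 413 days / 30.4375 = 13.57 months, and 103 / 13.57 = 7.59 per month (February start). 353 days / 30.4375 = 11.60 months, and 103 / 11.60 = 8.88 per month (April start).

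**Rate needed for no overlap at month 18.** With no start-up time: 300 / 36 = 8.3 per month, or 375 / 36 = 10.4. With 12 months of start-up: 300 / 24 = 12.5, or 375 / 24 = 15.6. Neither observed rate reaches 10.4.

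**Overlap.** Assume constant accrual r and a 5-year clock that starts L months before first enrolment. The article does not give L, so 0 to 12 is an assumed range. The number still in follow-up at month 54 is N − r × (36 − L) for month 18 and N − r × (42 − L) for the 12-month blood spot, floored at zero. Example: N = 375, February, L = 0 gives 375 − 7.59 × 36 = 102, or 27%.

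| N, enrolment start | Outcome | L = 0 | L = 6 | L = 12 |
|---|---|---|---|---|
| 375, February | 18-month | 102 (27%) | 147 (39%) | 193 (51%) |
| 375, April | 18-month | 55 (15%) | 109 (29%) | 162 (43%) |
| 300, February | 18-month | 27 (9%) | 72 (24%) | 118 (39%) |
| 300, April | 18-month | 0 (0%) | 34 (11%) | 87 (29%) |
| 375, February | 12-month spot | 56 (15%) | 102 (27%) | 147 (39%) |
| 375, April | 12-month spot | 2 (1%) | 55 (15%) | 109 (29%) |
| 300, February | 12-month spot | 0 (0%) | 27 (9%) | 72 (24%) |
| 300, April | 12-month spot | 0 (0%) | 0 (0%) | 34 (11%) |

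Counts are over all four arms. With 1:1:1:1 allocation throughout, the same share is expected in each arm.

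**Time to complete a programme.** Each programme takes six weekly sessions, so someone with only a few days of overlap is barely exposed. Requiring at least 42 days of overlap removes 103 / 413 × 42 = 10.5 people (February rate) or 103 / 353 × 42 = 12.3 people (April rate) from a non-zero cell. That trims the table but does not change the picture.

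**Dilution, illustration only.** Suppose a fraction f of SOC participants gains the full 20-point effect by month 18. The difference becomes 20 × (1 − f) points: 18 at f = 0.1 and 16 at f = 0.2. With an assumed 10% SOC uptake, 75 per arm and a two-sided .05 two-proportion test, power is 87% at f = 0, 78% at f = 0.1 and 66% at f = 0.2. A contrast of 150 against 150 starts at about 99% under the same rates and so has more to spare. The article gives neither f nor the SOC rate.

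**The case against.** The strongest reply is that the sentence describes a post-follow-up implementation phase. Its stated purpose is implementation data, and it says nothing was paid during that period, whereas surveys through month 18 were paid. Read literally, an unpaid period has to come after the paid month-18 survey. That reading is possible. The clause may equally mean only that sessions in this phase were unpaid, and the words on who was offered the interventions are universal. The ambiguity stands, and a sentence is needed to settle it.

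A second reply is that the article condenses a fuller protocol, which may hold the condition. It may. But the article states a positive rule with its own trigger and its own population; if the full protocol restricts that population, the published rule is wrong as written.

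Third, the timetable is not given. The article states neither the start of the 5-year clock, nor the planned end of enrolment, nor a planned accrual rate, and first-year accrual need not persist. With 300 enrolled, an April start and no start-up time, the last 18-month visit falls at 33.8 + 18 = month 51.8 and nobody overlaps. This stands, and it is why the result is a range that includes zero for 300.

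Fourth, a reader might infer that the trial's SOC data are contaminated, or that a definite amount of power is lost. The documents support neither. The award was terminated on 21 March 2025, 12 to 14 months after enrolment began, so the last 6 months of a 5-year study had not plausibly been reached. Any power figure rests on assumed acceptance, uptake and speed of effect. It also uses a single-visit comparison, whereas the primary model spans four time points and the earlier ones are largely unaffected.

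**Conclusion.** The point holds in conditional form. The offer is tied to calendar time and is open to every arm, with no stated requirement of completed follow-up. If enrolment runs past study month 36 (month 42 for the 12-month blood spot), late enrolees in arms A, B and C can cross over before their last outcome visits, and both factorial contrasts are biased towards no difference.

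At the reported accrual, with 0 to 12 months of start-up assumed, about 15-51% of 375 or 0-39% of 300 would still be in 18-month follow-up when the offer opens. For the 12-month blood spot the ranges are about 1-39% and 0-24%. For the planned 375, overlap at month 18 occurs even with no start-up time. The article describes start-up work with the community advisory board, so zero is the end of the range most favourable to the plan.

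These are shares exposed to the offer, not shares that would accept it. The weakness is in the design as published. It matters if the design is resumed or reused, and it is not evidence about the data collected before termination.

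**What to change.** Add one sentence: the implementation-phase offer is made to a participant only after that participant's final outcome assessment. This removes the overlap by construction, whatever the accrual.

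Record the offer date for every participant. For anyone offered earlier, censor outcome data from the randomised comparison at the offer date and treat later values as missing. Use the offer date and not the date of acceptance, because acceptance is a choice made after randomisation and would select. Since a calendar offer makes this missingness depend on enrolment date, enrolment date should enter the multiple imputation that the plan already foresees.

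The cost is one sentence and one date field. The downside is that some late enrolees are offered the interventions later, or not within the study, which also means somewhat less implementation data. Where censoring is used, late-visit information is lost for those participants.

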### Qualitative Data Collection

A subset of 40 TMSM, stratified by PrEP use, was to be purposively selected for IDIs (10 per study arm) at their 9-month visit. Sampling aimed to ensure that 50% of participants were BIPOC or Latine. Additional participants could be recruited as needed to achieve data saturation. IDIs were conducted as part of the 9-month study assessment—the acute postintervention time point—to maximize recall. IDIs explored participant decision-making and experiences with PrEP and the interventions. Interviews were conducted via an online video-conferencing platform (Zoom) [87]. Each IDI lasted approximately 60-90 minutes, followed a semistructured interview guide (Multimedia Appendix 2), and was to be conducted by an interviewer trained in qualitative research and experienced in working with transgender communities.

### Randomization and Blinding

Participants were randomized after their baseline HIV results were received and confirmed. Randomization was automated, computer-generated, and allocation sequences were concealed. Stratification was based on ethnoracial identity (BIPOC or Latine vs White) and MAP state LGBTQ equality policy tally (“high, medium, or fair” vs “low or negative” overall policy tally, as of October 2023; see Table S2 in Multimedia Appendix 1) [55]. The MAP state LGBTQ equality policy tally assesses over 50 LGBTQ-related laws and policies across US states (eg, nondiscrimination, health care access, religious exemptions, identity documents), providing a snapshot of the legal and policy climate for LGBTQ people [55]. Stratification was implemented to ensure balance across study arms and to facilitate subgroup analyses [88], given the disproportionate HIV burden among BIPOC or Latine versus White individuals [5] and the impact of repressive anti-LGBTQ policies on HIV prevention efforts [89]. Blinding was maintained at the statistician and investigator levels [90], but was not possible for participants or intervention staff.

### Training and Quality Assurance/Quality Control

All research staff completed extensive training on the study objectives, protocol, and intervention procedures. Additional training covered transgender health, HIV, PrEP navigation, mental health crisis management, substance use, harm reduction, trauma-informed care, and addressing experiences of violence. Intervention staff training included observing and conducting mock intervention sessions. A mental health clinician, who was both a consultant and a member of the community, was available on-call to provide regular clinical supervision. Staff were also trained in human participant protections, confidentiality and privacy, informed consent, and Good Clinical Practice in accordance with federal regulations. Refresher training was conducted annually. Laboratory testing followed standardized protocols and procedures. Surveys were administered using computer-assisted self-interview methods to ensure consistency and reduce social desirability bias. Instruments were piloted to maximize comprehension, and logic checks and skip patterns were employed to minimize data entry errors. Data were reviewed regularly to ensure consistency and accuracy.

### Intervention Fidelity

To ensure interventions were implemented as intended and core components were delivered according to protocol, intervention facilitators completed a checklist documenting their self-rated adherence to the intervention procedures. Session notes captured qualitative data on intervention implementation, including facilitator rapport, group dynamics, and other insights related to delivering manualized interventions. At the 6-month follow-up survey, participants reported on the intervention content they received and their experiences, including responses on the 8-item Client Satisfaction Questionnaire [91].

### Statistical Analysis

#### Power

Factorial trials can be powered to detect either main effects or interaction effects, depending on the anticipated influence of interactions within the trial context [92]. This trial was powered to detect the main effects of the PrEP4T and LS4TM interventions. The trial was not powered to detect a PrEP4T × LS4TM interaction effect because (1) based on our conceptualization, the interventions were distinct in delivery (individualized vs group based) and content (peer navigation vs. community support and IMB strategies), and informed by preliminary studies and knowledge of the study population, we did not anticipate a combined interaction effect; and (2) any potential interaction was expected to be negligible, described in factorial trials as a minor “small quantitative interaction” [92-94]. Both PrEP4T and LS4TM were distinct, peer-delivered digital interventions that TMSM endorsed for HIV prevention in our prior research. We hypothesized that each strategy would independently increase PrEP uptake by at least 20% among TMSM, addressing the main-effects research question. Although we did not anticipate interaction effects, we hypothesized additive effects such that participants assigned to the PrEP4T + LS4TM condition would achieve the highest PrEP uptake rates. These superiority hypotheses were supported by evidence from a systematic review of peer-delivered interventions [47].

We estimated PrEP uptake rates in the SOC condition based on prior TMSM data [8,15] and conducted simulations using an SAS macro [95]. Simulations varied the number of participants per condition (n=40-120) and the magnitude of intervention effects over 18 months (20%-40%) for the PrEP4T and LS4TM conditions. Assuming 10% attrition, a total sample size of 300 (75 per condition) provided 80% power or greater to detect a 20% increase in PrEP uptake for each intervention versus SOC at a .05 significance level. We selected a 20% increase because smaller differences were not considered clinically meaningful for potential scale-up. To account for attrition, we planned to enroll 375 participants at baseline, anticipating approximately 20% loss to follow-up, resulting in 300 participants completing the study.

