### Study Objective and Aims

The goal of the Transmasculine One-on-One and Group Empowerment for Targeted HIV Reduction (TOGETHR) study was to evaluate the effectiveness of digitally delivered individual and small-group peer-based strategies in improving PrEP uptake and adherence among at-risk, HIV-negative adult TMSM.

Applying the Healthcare Access [49], Gender Affirmation [7,51], and IMB [53] frameworks, we conducted a digital, open-label, randomized 2×2 factorial trial (1:1:1:1 allocation) of peer-delivered HIV prevention strategies to increase PrEP uptake among TMSM (n=300) residing in Ending the HIV Epidemic (EHE)–prioritized geographic hot spots in the United States. The specific aims were to:

Aim 1. Compare the efficacy of 4 peer-delivered HIV prevention strategies implemented over 6 weeks to increase PrEP uptake (primary outcome) among 300 PrEP-indicated, HIV-negative TMSM, which include(A) standard of care (SOC)digital PrEP locator and a library of syndicated HIV prevention, sexual health, and antistigma materials;(B) SOC + PrEP for transgender men and transmasculine people (PrEP4T; 1-on-1 PrEP peer navigation); (C) SOC + LifeSkills for Transgender Men and Transmasculine People (LS4TM; peer-delivered group-based PrEP behavioral intervention); or (D) SOC + PrEP4T + LS4TM.Hypothesis 1.1:Rates of PrEP uptake will be higher in (B) SOC + PrEP4T and (C) SOC + LS4TM conditions compared with (A) SOC (main effects).Hypothesis 1.2:PrEP uptake rates will be highest for participants randomized to (D) SOC + PrEP4T + LS4TM compared with (A) SOC (additive effects).Aim 2. Examine the mechanisms through which PrEP4T and LS4TM impact PrEP uptake using causal mediation analysis.Hypothesis 2.1:Health care access empowerment, transgender community support for gender affirmation, and IMB constructs will mediate the relationship between PrEP4T, LS4TM, and PrEP uptake.Aim 3. Explore PrEP decision-making processes and intervention experiences through in-depth interviews (IDIs; n=40; 10 per condition) to inform future scale-up and implementation of these interventions.

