#### Condition D (SOC + PrEP4T + LS4TM)

This is an online peer-delivered combined intervention. Participants in this arm received both PrEP4*t* (1-on-1) and LS4TM (group-based) interventions in addition to SOC. Group D received a total of 21 hours of content, consisting of six 2-hour LS4TM sessions and six 1.5-hour PrEP4T sessions. These interventions were not delivered simultaneously within the same 6-week period.

**Table 2 table2:** PrEP4T^a^ intervention sessions: session number, title, content, and conceptual framework guiding the intervention sessions.

Session number	Session title	Session content	Conceptual framework
1	Introduction, Background, and Goal Setting	Build rapport with the participant Assess the participant’s background and sexual health history. Set a realistic, sexual health–related goal for the program (eg, to start PrEP^b^, to consistently communicate with partners about sexually transmitted infection testing). Discuss factors that may impact risk for HIV among transgender men and transmasculine people.	IMB^c^ and Gender Affirmation
2	HIV Transmission and Prevention	Assess what participants know about HIV prevention and how they currently put that information into practice. Introduce participants to the concept of harm reduction. Fill in knowledge gaps and answer questions about HIV prevention. Build on or reinforce participants’ existing harm reduction strategies.	IMB and Healthcare Accessibility
3	Accessing PrEP and Preventive Health Care	Discuss barriers to accessing PrEP and work with participants to identify solutions and options available to them. Provide a brief overview of where and how participants can access postexposure prophylaxis. Discuss preventive health care access, with an emphasis on primary care and sexually transmitted infection testing. Address other preventive care topics, including vaccinations (human papillomavirus, hepatitis A and B), contraception, cervical and anal Papanicolaou testing, and gender-affirming care.	IMB and Gender Affirmation Healthcare Accessibility

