3	PrEP^c^ for Pleasure	Inform participants about PrEP, postexposure prophylaxis, and contraception. Encourage participants to consider whether PrEP may be right for them. Identify barriers to PrEP use and uptake, and ways to navigate these.	IMB and Healthcare Accessibility
4	Barriers and Opportunities	Learn about setting attainable goals and set a personal goal. Identify roadblocks and structural barriers that impact individual and collective goals and constrain decision-making. Discuss support and resources that can help to overcome roadblocks and barriers to achieving goals.	IMB and Healthcare Accessibility
5	Communication and Partner Negotiation	Identify our rights and responsibilities in relationships. Discuss a variety of partner communication topics relevant to transgender men and transmasculine people, including meeting partners, disclosing identities, educating partners about our transgender identities, and establishing consent and boundaries. Brainstorm and practice healthy partner communication and negotiation skills.	IMB and Gender Affirmation
6	Tying It All TOGETHR^d^	Highlight general sexual health concerns for transgender men and transmasculine people, including healthy sexuality and sexual pleasure. Review the program, then revisit and revise goals moving forward. Gather feedback from participants on the program, the curriculum, and how it was delivered.	IMB

^a^LS4TM: LifeSkills for Transgender Men and Transmasculine People.

^b^IMB: Information, Motivation, and Behavioral Skills.

^c^PrEP: preexposure prophylaxis.

^d^TOGETHR: Transmasculine One-on-One and Group Empowerment for Targeted HIV Reduction.

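### The no-interaction premise leans on distinct content that Tables 2 and 3 contradict, and the claim that the combined arm is best and additive is tested only against SOC

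*Protocol article*

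**What the plan says.** The Power section says the trial is powered for the main effects of PrEP4T and LS4TM and not for their interaction. It gives as grounds that "the interventions were distinct in delivery (individualized vs group based) and content (peer navigation vs. community support and IMB strategies", along with preliminary studies, knowledge of the population, and an interaction expected to be negligible. On sample size it states that "a total sample size of 300 (75 per condition) provided 80% power or greater". The purpose of that power is given as "to detect a 20% increase in PrEP uptake for each intervention versus SOC", with the test level set to .05 and 10% attrition allowed for.

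The contents of the two programs are set out in Tables 2 and 3. Session 1 of each contains the same sentence: "Discuss factors that may impact risk for HIV among transgender men and transmasculine people". Session 3 of PrEP4T includes "Discuss barriers to accessing PrEP and work with participants to identify solutions and options available to them"; session 3 of LS4TM includes "Identify barriers to PrEP use and uptake, and ways to navigate these". Hypothesis 2.1 states that "Health care access empowerment, transgender community support for gender affirmation, and IMB constructs will mediate the relationship between PrEP4T, LS4TM, and PrEP uptake".

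On the combination, Hypothesis 1.2 and the Power section expect uptake to be highest in arm D and call the effects additive. In Data Analysis by Aim, the primary model has a four-level condition variable with SOC as reference, crossed with time. The contrasts it names are therefore B, C and D, each against A.

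**The concern.** The stated rationale gives IMB strategies and community support to LS4TM and peer navigation to PrEP4T. If the two programs in fact teach much of the same material and work through the same mediators, the second program may add less to the first than it achieves alone. Content then no longer supports the expectation of no interaction.

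Two results depend on that expectation. A main effect taken at the factorial margins is the average of a program's effect without and with the other program, so a shortfall in D pulls it down along with its power. The claim that the combination is highest and additive also needs evidence about what D adds to B and to C. A comparison of D with SOC cannot supply this, because D can beat SOC comfortably on the strength of one program alone.

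**Working it through.** **1. Content, side by side (Tables 2 and 3).**

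| Item | PrEP4T | LS4TM |
|---|---|---|
| IMB listed as framework | sessions 1–6 (6 of 6) | sessions 2–6 (5 of 6) |
| HIV risk factors (same sentence) | session 1 | session 1 |
| HIV transmission | session 2 | session 2 |
| PrEP barriers and solutions | session 3 | session 3 |
| Postexposure prophylaxis, contraception | session 3 | session 3 |
| Goal setting | session 1 | session 4 |
| Partner communication | session 4 | session 5 |
| Support and resources | session 5 | session 4 |

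The session titled Social Support belongs to PrEP4T. The split in the Power section does not match these tables.

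**2. Inputs.** From the Power section: 75 per arm, 10% attrition (75 × 0.9 = 67.5 analysed), a 20% increase per intervention, and a .05 level. Assumed here: 20% means 20 percentage points, the test is two-sided, there is a single time point, additivity is on the risk-difference scale, and SOC uptake p is 10% to 40% (the article does not give it). Cells: A = p, B = C = p + 0.20, D = p + 0.40 − s, where s is the shortfall from additivity.

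**3. The plan's own figure.** Its simulation cannot be reproduced without the SOC rate. Two approximations bracket it.

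- *Each arm versus SOC*: SE = √{[A(1−A) + B(1−B)]/67.5}. At p = 20%: √(0.40/67.5) = 0.077; 0.20/0.077 = 2.60; power = Φ(2.60 − 1.96) = 74%. For p = 10%, 20%, 30%, 40% the power is 85%, 74%, 68%, 66%.
- *Factorial margins, additive*: effect = [(B−A) + (D−C)]/2 and SE = ½√{Σ pᵢ(1−pᵢ)/67.5}. At p = 20%: ½√(0.88/67.5) = 0.0571; 0.20/0.0571 = 3.50; power 94%. Over p = 10% to 40% it is 93% to 97%.

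The stated 80% or more fits the margins at every assumed SOC rate. It fits the single-arm contrast only at low SOC rates.

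**4. Effect of a shortfall in D.** B−A and C−A do not contain D, so neither their estimates nor their power change. At the margins:

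| D relative to additive | Marginal effect | Power, p = 10% / 20% / 30% / 40% |
|---|---|---|
| Additive (s = 0) | 20 points | 97% / 94% / 93% / 94% |
| 10 points short | 15 points | 81% / 74% / 72% / 72% |
| No better than one program (s = 20 points) | 10 points | 49% / 42% / 39% / 39% |

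**5. What D versus A can show.** If D is no better than one program, D = p + 0.20, and D versus A has the same effect and variance as B versus A in step 3. It is significant 85%, 74%, 68%, 66% of the time for p = 10% to 40%. A pooled-variance test gives 84% down to 65%. A significant D versus A therefore does not separate an additive combination from one that adds nothing.

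**6. Precision on the interaction.** At p = 20% under additivity, the SE of (D−C)−(B−A) is √(0.88/67.5) = 0.114, so the 95% half-width is 1.96 × 0.114 = 0.22, or about ±22 points. D versus B has SE √(0.48/67.5) = 0.084; if D is fully additive, 0.20/0.084 = 2.37 and power is about 66%.

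**The case against.** The strongest reply is that the planned analysis does not use the margins. Power is stated for each intervention versus SOC, Hypothesis 1.1 compares B and C with A, and the model uses SOC as reference. This stands. A reader might infer from the content overlap that the single-program estimates are biased or that the stated power is lost. The documents do not support that: B−A and C−A are unaffected by anything that happens in D.

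Second, overlap is not evidence of sub-additivity. This also stands. The framework column names guiding theory, not identical material. PrEP4T is individualized navigation, LS4TM is group work with identity and stigma content, and the two were not delivered in the same 6 weeks, so repetition could reinforce. Delivery format, preliminary studies and population knowledge remain as stated grounds.

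Third, the margins figures depend on the number analysed. With 75 per arm, since 375 are to be enrolled so that 300 complete, a 10-point shortfall leaves 76% to 85% power. The 80% level is crossed at a shortfall of about 8.5 to 12 points, against about 7 to 10 with 67.5. The figures are illustrations, not thresholds to adopt.

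Fourth, Hypothesis 1.2 is formally D versus A, and declining to power for interaction is an openly declared choice. Both are true. But the hypothesis and the Power section also say highest and additive, and D versus A addresses neither word.

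**Conclusion.** The concern holds in limited form. The content part of the no-interaction rationale conflicts with Tables 2 and 3 and with Hypothesis 2.1. Sub-additivity is plausible but not demonstrated, and the single-program comparisons with SOC are sound either way.

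Two consequences remain. Because the Power section speaks of main effects but states the contrast as each intervention versus SOC, it is unclear whether the 80% depends on near-additivity. If it refers to the margins, power ranges from 93%–97% (additive) to 39%–49% (D no better than one program). Also, the planned comparison for D cannot carry the claim made for it: it would be significant about 66% to 85% of the time with no added benefit over one program.

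These figures rest on 67.5 per arm, SOC uptake of 10% to 40%, a 20-point single-program effect, a two-sided .05 test and one time point. The planned model works on the log-odds scale with repeated measures, so its exact figures will differ.

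**What to change.** In the Power section:
- Replace the distinct-content rationale with one consistent with Tables 2 and 3, keeping the other grounds if they are considered sufficient.
- State whether the 80% refers to each arm versus SOC or to the factorial margins, and give the SOC rate used.
- If it refers to the margins, say that it assumes near-additivity and show power over a range of shortfalls.

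In Data Analysis by Aim:
- Add D versus B, D versus C, and the PrEP4T × LS4TM interaction on the risk-difference scale with a 95% confidence interval.
- Base any statement that D is highest or additive on these, not on D versus A. A non-significant interaction should not be read as additivity.
- Describe any marginal effect as an average over the other program.

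The cost is wording and a few contrasts from data already to be collected. The power statement may become less favourable, and the interval for the interaction will be wide (about ±22 points at SOC 20%), so the conclusion about the combination may have to be modest.
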